### Data management and analysis

It is planned that anonymous data and all appropriate documentation will be kept securely for the defined period required from the relevant ethics committees. Participants will be clearly informed that their data will be used for the stated purposes of the study. Only members of the study team and its support staff will see the data. A full clinical Data Management Plan will be written by the trial team before recruitment commences, which will include a privacy impact assessment. All paper-based data will be double entered. Data will be entered into a secure Electronic Data Capture System (EDC). This database is built to validated standards and maintained and managed by the UKCRC registered Exeter Clinical Trial Unit.

Data from questionnaires will be anonymised through the use of unique participant identification codes when entered into computers for statistical analysis.

Qualitative data from the interviews will be transcribed verbatim and then anonymised through the removal of people’s names and other personal information; where necessary non-identifiable terms or pseudonyms will be used instead. In reports of the work, where excerpts are quoted from interviews, any information that might lead to the identity of participants, other people or organisations being inferred will be disguised.

All data will be collected and stored in accordance with data protection regulations in the individual countries. Data will be stored electronically on computers and access will be controlled via passwords and permissions to dedicated study folders. Hard copies of questionnaires will be securely stored in locked filing cabinets in offices that are accessible only to research staff. Information used in the administration of the study, including participants’ names and addresses, will be stored separately from the research data and used only to maintain contact with participants. Administrative databases will be held at the study centres.

The CI will preserve the confidentiality of participants taking part in the study and is registered under the EU GDPR (General Data Protection Regulation (Regulation (EU) 2016/679)). The research will follow GDPR guidance. Only members of the research team will have access to the original data, which will be stored in a locked filing cabinet. Participants’ personal details will be stored separately from the original data, and will be kept in a separate file on a password protected computer at the study sites. Access to data will be limited to quality control, audit, and analyses. Data shared between sponsor and co-investigators will be de-identified to minimise breach of confidentiality. Each participant will be assigned an identification code, which will be used in all data storage files; these will not contain names or any other means of personal identification. All personal details will be deleted on completion of the study.

### Statistical analysis

All outcome measures will be reported at baseline, after the intervention (follow up 1) and at 6-months after follow-up 1 (follow up 2). Baseline characteristics (age, gender, ethnicity, civil status, education, living situation, use of medication) will be presented for each intervention group and by site. Trial analysis will include all participants with allocation to study arms as randomised, i.e. on an intention-to-treat basis.

The primary outcome measure (GSES) [39] will be analysed using the multilevel modelling approach to analysis of covariance (ANCOVA), i.e. with follow-up GSES as dependent variable and with study arm, site Norway 1, Norway 2, UK and Australia, baseline GSES, time since baseline assessment, other baseline variables predictive of the outcome, as well as potential variables constituting baseline imbalance between study arms, as independent variables, while allowing for clustering within treatment groups [57]. The estimate of the effect of the intervention will be reported with a 95% confidence interval and associated *p*-value. Missing outcome data will be handled by including any variables predictive of missingness in a complete case-analysis of the multilevel ANCOVA model [58]. The estimate of the effect of the intervention will be reported with a 95% confidence interval and associated *p*-value. Secondary outcomes will be analysed similarly.

Multiple imputation (MICE) will be used for sensitivity analysis to assess the robustness of the results to differential loss to follow up [58].

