### Sample size

The sample size calculation is based on the approach outlined in Lohr et al. [35] and the aim of detecting a standardised mean difference of 0.4 in the General Self-Efficacy Scale (GSES) between the intervention and control arms of the trial, with 90% power at the 5% significance level. An effect size (Cohen’s D) of 0.4 is a commonly used threshold for clinical meaningfulness [36]. A standard sample size calculation suggests that 268 participants would be required (134 participants per arm). Including in the analysis covariates that are predictive of the outcome will increase the precision of the effect estimate and hence the statistical power. Assuming a coefficient of determination R2 of 0.25 for the regression of the outcome on baseline variables, the required total sample size is reduced to 201 [37].

Due to the potential for a clustering effect in the intervention because participants are attending group sessions where the outcomes for individuals nested within the same educational groups [WS8] are likely to be more similar than the outcomes for individuals within different groups, the variance in the intervention arm will be inflated. We assume a residual intra-cluster correlation coefficient (ICC) of 0.1. We plan for group sizes of 8 in the intervention arm and an allocation ratio of 2:1 (i.e. 67% of participants will be allocated to the treatment arm). Assuming 25% attrition we anticipate an average number of 6 participants within each cluster contributing data for analysis. Given this plan, and allowing for attrition, we will need to recruit a total of 246 participants to the intervention arm and 123 participants to the TAU arm in order to provide sufficient power for the primary analysis. Harmonising to a fixed block size we will recruit 248 participants to the treatment arm and 124 participants to the control arm, i.e. a total of 372 participants. Additional allowance for varying group sizes is not necessary if the coefficient of variation in cluster sizes is smaller than 0.23 [38], which we expect to be the case in this study design.

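### Covariates added for missingness are not limited to baseline, and no stated analysis departs from missing at random, so outcome-dependent loss goes untested

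*Protocol article*

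**What the plan says.** The Statistical analysis section of the protocol article sets a multilevel ANCOVA of follow-up GSES. Its covariates are arm, site, baseline GSES, time since baseline assessment, other baseline variables that predict the outcome, and variables imbalanced at baseline. On missing data it adds: "Missing outcome data will be handled by including any variables predictive of missingness in a complete case-analysis of the multilevel ANCOVA model". The one sensitivity analysis named is this: "Multiple imputation (MICE) will be used for sensitivity analysis to assess the robustness of the results to differential loss to follow up". The section opens with the analysis population: "Trial analysis will include all participants with allocation to study arms as randomised, i.e. on an intention-to-treat basis".

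The Sample size section plans for the loss: "Assuming 25% attrition we anticipate an average number of 6 participants within each cluster contributing data for analysis". It does not split attrition by arm. The Randomisation section says that participants, care partners and facilitators are not blinded, and Table 2 lists the participant as the informant for GSES. The Outcome section puts follow-up 1 after the intervention and follow-up 2 six months later. No imputation model is described, and no analysis is described in which unseen outcomes may differ from what the observed data predict.

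**The concern.** There are two separate problems.

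**The covariate rule.** The covariates chosen to predict the outcome are explicitly baseline variables. The missingness sentence drops that limit and puts its variables into the model that estimates the effect. Which variables predict missingness is known only after follow-up, so the choice is also data-driven. A post-randomisation variable that treatment has changed, such as follow-up 1 GSES in a follow-up 2 model, would satisfy the rule. Conditioning on it takes out the part of the effect that runs through it.

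**The robustness check.** Covariate-adjusted complete cases and standard MICE both assume missing at random. If they use the same variables, they will agree whether or not dropouts did worse than predicted, and that agreement would be reported as robustness to differential loss. The outcome is self-reported by people who know their arm, and only one arm is asked to attend ten weekly sessions. Reasons for leaving could therefore plausibly differ by arm and relate to outcome.

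**Working it through.** **Inputs from the Sample size section.** Effect 0.4 SD, "with 90% power at the 5% significance level" (two-sided assumed), R² 0.25, ICC 0.1, groups of 8, 248 vs 124 recruited, 25% attrition.

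**The plan's own figures.** The normal formula gives 2(1.960 + 1.282)²/0.4² = 131.4, so 132 per arm and 264 in total, against 268 stated. Then 268 × (1 - 0.25) = 201, as stated. A partially nested calculation with 6 analysed per group and cluster variance added to the residual gives 361 recruited, against 369 stated (within 3%). The sample size is not in dispute.

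**1. Adjusting for follow-up 1 GSES in a follow-up 2 model.** Assume a true effect of 0.4 SD at both visits, within-arm correlation r between follow-up scores, and correlation 0.5 of baseline with each (0.5² = 0.25, the plan's R²). With baseline already in the model, the slope on follow-up 1 is b = (r - 0.5²)/(1 - 0.5²) = (r - 0.25)/0.75, and the remaining effect is 0.4(1 - b).

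| r | b | effect left |
|---|---|---|
| 0.5 | 0.333 | 0.27 |
| 0.6 | 0.467 | 0.21 |
| 0.7 | 0.600 | 0.16 |

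**2. Complete cases against MICE.** The check used 1,500 simulated trials of 248 vs 124 with true effect 0.40, R² 0.25, ICC 0.1 in the intervention groups and 5 imputations. Point estimates came from single-level least squares (Monte Carlo error about 0.003). The dropout mechanisms are assumptions. In the second and third rows, loss depends on the named factor in the intervention arm only.

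| Loss depends on | Loss, intervention / TAU | Complete case | MI, same variables | MI with post-baseline auxiliary |
|---|---|---|---|---|
| arm and baseline | 32% / 24% | 0.398 | 0.398 | 0.398 |
| an observed post-baseline variable | 30% / 17% | 0.539 | 0.538 | 0.406 |
| the unseen outcome | 30% / 17% | 0.618 | 0.617 | 0.546 |

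**3. Size of bias under outcome-dependent loss.** If dropouts score d SD lower than missing at random predicts, both methods overstate the effect by pI·dI - pC·dC, where p is the loss in each arm.
- 30% vs 15% loss, d = 0.2 to 0.6 in both arms: 0.15 × d = 0.03 to 0.09 SD.
- The same loss, d in the intervention arm only: 0.30 × d = 0.06 to 0.18 SD.
- 20% vs 35% loss, d in both arms: -0.03 to -0.09 SD, so the direction is not fixed.
- 25% in each arm with equal d: zero.

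**4. Tipping point.** With 25% loss, 186 and 93 are analysed. SE = √[(0.75/0.9)(1.5)/186 + 0.75/93] = 0.1216, where 1.5 = 1 + (6 - 1) × 0.1. For an observed effect of 0.4, the lower 95% limit is 0.4 - 1.96 × 0.1216 = 0.162. A shift of delta in intervention dropouts alone moves the effect by 0.25 × delta, so significance is lost at a shift of 0.162/0.25 = 0.65 SD below prediction (0.67 if cluster variance is taken within the residual, SE 0.1188). For an observed 0.3, the same sum gives 0.25 to 0.27 SD.

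**The case against.** The strongest defence is that this is a condensed article. The imputation model and any delta analysis may sit in a statistical analysis plan that is not shown. MICE with post-baseline auxiliaries rests on a weaker assumption than complete cases, and it recovered 0.406 in the second scenario. That stands, and for this reason the missing imputation detail is not the point. The point is what the article states: an open covariate rule in the effect model, and a method offered as the check on differential loss that, by default, does not leave missing at random. Even with the auxiliary, the third scenario gave 0.546.

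Some stronger readings are tempting but not supported:
- *Differential loss is neither handled nor tested.* The first scenario contradicts this. Loss that differs by arm but depends on arm and adjusted baseline variables leaves the estimate unbiased (0.398).
- *Session attendance will be adjusted for.* It is recorded only for people offered sessions, so it cannot be an ordinary covariate across both arms. Nor does the article say that follow-up 1 GSES will enter a follow-up 2 model; the wording merely permits it.
- *The effect would fall to 0.20, 0.16 or 0.12 SD*, from 0.4(1 - r). That omits baseline GSES, which the model always contains.
- *Complete cases contradict intention to treat.* The sentence mainly means analysis by allocated arm, and the Sample size section openly plans for 25% not contributing data (93 of 372). Someone seen only at follow-up 1 is not said to be dropped from a follow-up 1 analysis.
- *The primary model must be replaced by a likelihood-based one.* That is a preference, not a correction.

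**Conclusion.** The point holds in a limited form. As worded, the missingness rule allows treatment-affected variables into the effect model. In the follow-up 1 GSES example, that would leave about 0.27 to 0.16 SD of a true 0.4, under the assumed correlations. Separately, no stated analysis allows dropouts to differ from what the observed data predict. With the same variables, MICE reproduces the complete-case estimate to within 0.001 in all three scenarios, including two where both are well above the truth.

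The simulated biases (about 0.14 and 0.22 SD) illustrate mechanisms and do not forecast this trial; no dropout pattern by arm is given. An observed effect of 0.4 is fairly resilient, since it takes intervention dropouts about 0.65 SD worse than predicted to lose significance. A smaller observed effect would be much less so. This is a worthwhile, inexpensive tightening, not a flaw that undermines the design.

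**What to change.** 1. Apart from the time term already listed, limit covariates in the effect model, including those added for missingness, to pre-randomisation variables named before unblinded data are seen.
2. Use post-baseline predictors of dropout and the other follow-up scores only as auxiliary variables inside MICE, never as covariates in the effect model.
3. Add delta-adjusted MICE with shifts set separately by arm, and report the tipping point. The range must be wide enough to reach it: about -0.65 SD in intervention dropouts for an observed effect of 0.4, SE about 0.12 and 25% loss. A range ending at -0.5 SD would stop short, because the effect would be 0.4 - 0.25 × 0.5 = 0.275 with lower limit 0.275 - 0.238 = 0.037.
4. Describe ordinary MICE as a check under missing at random, and the delta analysis as the check on outcome-dependent loss.

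The cost is a few sentences and slightly more analysis. No new data are needed, and neither the sample size nor the primary ANCOVA changes.

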### Qualitative analysis

Qualitative data will be analysed by way of systematic text condensation [59]. This approach involves the following steps in the analysis process: (1) establishing an overall impression of the data material and identifying preliminary themes by reading through the transcripts several times; (2) identifying and sorting units of meaning into code groups; (3) condensing the contents of each of the coded groups into subgroups; and (4) summarising and re-contextualising the contents of each code group to generalise descriptions and concepts. Malterud [59] argues that the data analysis will benefit from being conducted by more than one researcher; thus all transcripts will be read by several members of the research team to get an overall impression of the full data material, as in step (1) above. This step of the analysis requires the researcher to read with an open mind from a bird’s-eye perspective all pages within the transcripts, and then ask which preliminary themes (usually four to eight themes) can be identified in the material.

### User involvement

People with dementia, care partners and group facilitators from earlier health promotion groups [25] will be involved in all levels and all phases of the study including research planning, delivery and dissemination, and there will be extensive use of co-design groups and close collaboration with organisations representing people with dementia. This will ensure that the development and delivery of the integrated intervention for people with dementia and their families is centred around the needs of people with dementia themselves in all of the participating countries. Each site will appoint a user representative as a member of the respective research teams. This will ensure that perspectives from people with dementia, care partners and group facilitators from earlier health promotion groups are included and addressed throughout the trial.

### Study management

This study will be managed by the chief investigator ([name]), the trial manager ([name]) and the Programme Management Group (PMG), as part of the overall SHAPE programme. The PMG will be chaired by [name], Clinical Trial Unit, Exeter University and involve all the PIs, the trial manager and a consumer representative. The group will meet at 3 monthly intervals and additionally as required. Part of the remit of the PMG will be to oversee overall progress of the programme and monitor progress against milestones. Any discrepancy from milestones will be highlighted and a plan, developed to address the difficulties, will be instigated. For the purposes of this trial, the PMG will be acting as the Trial Management Group (TMG), with direct oversight of and responsibility for this study. The trial manager will send a written report to the chair of the PMG before each TMG meeting, detailing progress.

The day-to-day management of the trial will be conducted by the trial manager, [name], who will be supervised (weekly) and line managed by [name]. Additional supervision will be organised as needed, and major decisions will be discussed with PI group and PGM group, as appropriate.

### Indemnity

Each participating site will be responsible for providing indemnity to meet the potential legal liability of investigators/collaborators arising from harm to participants in the conduct of the research. No provision is made for non-negligent liability, which will be covered by usual procedures by the care provider as applicable.

### Publication and dissemination strategy

The study’s Dissemination and Publication Policy will be developed by the trial team and approved by the PMG as part of the Publication strategy for the whole SHAPE programme. To ensure authorship eligibility the Vancouver recommendations will be used. Scientific outputs, the use of the networking opportunities afforded by each country and making direct contact with local Commissioners will all ensure dissemination. A full and open publication of the results will be provided through peer-reviewed scientific journals. Additional communication will be undertaken through the web pages of the EU JPND, Stavanger University Hospital, Ageing and health, University of Exeter, Alzheimer’s Society and University of New South Wales.

## Discussion

The integrated SHAPE intervention represents a novel and different approach combining self-management and health promotion for people with dementia and e-learning for care partners. It is based on health promotion and self-management and on the imperative to maintain the dignity and autonomy of the person with dementia and support him or her in planning for the future together with the family. The adjunctive e-learning platform will provide care partners with the same information that the person with dementia receives plus some additional material and signposting to support them in their role. This will further empower the whole family to support and enable more effective self-management by the person with dementia, and enhance their ability to plan ahead together and make key decisions jointly - such as how and when to communicate their needs to health care services and to receive appropriate care at the right time. Being able to talk openly about the disease process and future challenges with family members in the early stage of the disease can be empowering for everyone involved. The website with the e-learning resources provided to the care partners will collect information on website use. The e-learning component will also be created in a version which does not collect any data on the user. The purpose of this is so it can be distributed to other people in the support network of the person with dementia, and it therefore has the potential to reach those who live in regional, rural and remote areas.

### Trial status

At the time of submission of this protocol paper (protocol version 6, dated 10.03.2020) was not open to recruitment. Recruitment is scheduled to start in November 2020, providing the COVID-19 pandemic situation allows this, and to be completed by January 2022.

## Data Availability

Not applicable.

## Abbreviations

AH: Norwegian national advisory unit on ageing and health
AE: Adverse event
ANCOVA: Analysis of covariance
CDR: Clinical dementia rating
AU: Australia
CI: Chief investigator
CSDD: Cornell scale for depression in dementia
CSRI: Client service receipt inventory
DSM: Diagnostic and statistical manual of mental disorders
DEMQOL: Measure of health related quality of life for people with dementia
EDC: Electronic data capture system
FAQ: Functional activities questionnaire
FU: Follow-up
GCP: Good clinical practice
GDPR: General data protection regulation
GP: General practitioner
GSES: General self-efficacy scale
ICC: Intraclass correlation coefficient
IDMC: Independent data monitoring committee
JPND: EU joint programme for neurodegenerative diseases
MCI: Mild cognitive impairment
MICE: Multiple imputation
MMSE: Mini mental state examination
NHS: National health service
NPI-Q: Neuropsychiatric inventory questionnaire
NRES: National research ethics service
NSW: New South Wales university
PI: Principal investigator
PMG: Programme management group
QALY: Quality adjusted life year
RCT: Randomised controlled trial
RSS: Relative‘s stress scale
SAE: Serious adverse event
SHAPE: Self-management and health promotion in early-stage dementia with E-learning for carers
SUH: Stavanger university hospital
TAU: Treatment as usual
TMG: Trial management group
UK: United Kingdom
UKCRC: UK clinical research collaboration
UNSW: University of New South Wales
